#### Criteria for discontinuing or modifying allocated interventions {11b}

Participants who fail to complete the study for various reasons or use prohibited drugs in the protocol, regardless of the time or reason, will be allowed to discontinue the study. Serious adverse events will be reported according to standard reporting requirements. The last recorded data for these participants will be included in the data analyses. Data obtained from participants who used prohibited drugs in the protocol will be treated as invalid. For participants who discontinue the trial, the researcher will record in detail the time and reason for discontinuation in the case report form (CRF).

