### Outcomes {12}

#### Primary outcome

The primary outcome of the trial is the efficacy of the Longmu Tang granule in improving the clinical symptoms of patients with AD after 8 weeks of treatment. The main evaluation of the primary outcome will be the change in the SCORAD score [18] from baseline to the end of the 8-week treatment. SCORAD was proposed by the European Task Force on AD. SCORAD includes the area (A) and severity (B) of skin lesions and the subjective symptoms of pruritus and their effects on sleep (C). The *SCORAD* system is internationally recognised as the gold standard for AD scoring. The SCORAD score ranges from 0 (best) to 103 (worst), with a minimal clinically important difference (MCID) of 8.7 [19]. Higher scores indicate more severe symptoms. The SCORAD scores of the participants before and after treatment will be statistically analysed.

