#### Participant timeline {13}

The visit schedule for all assessments (baseline, primary outcome, secondary outcomes, exploration outcomes, and security indicators) is shown in Fig. 1. At each assessment timepoint, the same investigator will evaluate the participants. During the treatment period (i.e. from baseline to week 8), all combined therapeutic medicines will be recorded, including their name, dose, and course. Participants’ expectations of the Longmu Tang granule will be assessed at baseline. The primary outcome and CDLQI score will be evaluated at baseline and at the first, second, fourth, sixth, and last visits. Exploratory outcomes, NCT scores, and safety indicators will only be evaluated at baseline and at the last visit. Table 4 summarises the schedule of screening, enrolment, intervention, assessments, and data collection.

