#### Sample size {14}

The sample size was calculated based on the primary outcomes, which were the change in the SCORAD score from baseline to the end of week 8. In our pilot trial [17], with 20 patients in the Longmu Tang group and 20 patients in the control group, the mean (± standard deviation) reductions in the SCORAD score after 8-week treatment were 20.76 ± 8.05 and 6.35 ± 8.69 in the Longmu Tang and control groups, respectively. In a previous study [22], the mean reduction in the SCORAD score in the Longmu Tang group was 15, with 31 patients in the Longmu Tang group and 31 patients in the control group. In another previous study [23], the mean reduction in the SCORAD score in the Longmu Tang group was 12.86, with 62 patients in the Longmu Tang group and 60 patients in the control group. Considering the three trials and number of patients in each of the three trials, we estimated the mean (± standard deviation) reduction in the SCORAD score after 8-week treatment in the experimental and control groups to be 15 ± 8.69 and 6.35 ± 8.69, respectively. Assuming an alpha risk of 5% and beta risk of 10% using the GPOWER software (version 3.1.9.7), a sample size of 46 (23 participants in each group) was calculated. Considering a 20% loss to follow-up, this trial will require 60 participants (30 participants in each group).

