#### Methods in analysis to handle protocol non-adherence and any statistical methods to handle missing data {20c}

Participants with poor adherence and a drug compliance < 80% or those who are no longer receiving medication and undergoing testing during the study will be included in the intention-to-treat analysis and excluded from the per-protocol analysis. A multiple data imputation procedure will be used to impute the missing data.

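### Two unreconciled rules can apply to the same missing week-8 SCORAD values: last recorded data in {11b}, multiple imputation in {20c}

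*Protocol article*

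**What the plan says.** All references are to the protocol article.

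- **Primary outcome:** "the change in the SCORAD score [18] from baseline to the end of the 8-week treatment".
- **Criteria for discontinuing or modifying allocated interventions {11b}:** the group concerned is "Participants who fail to complete the study for various reasons or use prohibited drugs in the protocol, regardless of the time or reason". For them, "The last recorded data for these participants will be included in the data analyses". The sentence after that reads: "Data obtained from participants who used prohibited drugs in the protocol will be treated as invalid".
- **Protocol non-adherence and missing data {20c}:** participants with poor compliance, or who have stopped medication and testing, "will be included in the intention-to-treat analysis and excluded from the per-protocol analysis". Then: "A multiple data imputation procedure will be used to impute the missing data".
- **Participant timeline {13}:** "The primary outcome and CDLQI score will be evaluated at baseline and at the first, second, fourth, sixth, and last visits".
- **Drop out criteria:** lack of benefit and adverse reactions are named among the reasons for voluntary withdrawal.
- **Sample size {14}:** expected SCORAD reductions are 15 and 6.35, each with SD 8.69. "Considering a 20% loss to follow-up, this trial will require 60 participants".

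**The concern.** A child who stops before week 8 has no week-8 SCORAD but, in most cases, has one or more earlier scores. Section {11b} sends the last of these into the analysis. Section {20c} keeps the same child in the intention-to-treat set and calls for the gap to be multiply imputed. Neither section mentions the other, and neither limits itself to an endpoint, an analysis set or a sensitivity analysis. Two competent analysts could therefore reach different primary results from this text, and the choice could be made after the data are seen.

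The rules also differ in what they assume. Substituting the last value supposes no further change after leaving, whereas the planning figures expect change over the full 8 weeks. With withdrawal foreseen for poor efficacy and adverse reactions, the amount and timing of loss may differ between arms, so the direction of any error cannot be fixed in advance.

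This is not detail left to an unseen analysis plan. The article states both rules, and a plan that followed substitution for the primary analysis would depart from {20c}, just as one that followed imputation would depart from the plain reading of {11b}.

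**Working it through.** **1. The plan's own figures.** The planned difference is 15 − 6.35 = 8.65, with SD 8.69, two-sided alpha 0.05 and power 0.90. The noncentral t distribution gives power 0.897 with 22 per group and 0.910 with 23, so 23 per group (46 in all) reproduces. Allowing for 20% loss, 46 / 0.8 = 57.5, or 58. The stated 60 is within two participants of that. The sample size is not in question here.

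**2. How many values are affected.** 0.20 × 60 = 12. This is an upper figure, because {14} does not say that all the loss falls before week 8 and follow-up runs for 8 weeks after treatment.

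**3. Effect of substituting the last value.** Let d_L and d_P be the proportions lost on Longmu Tang and placebo, and f the share of the eventual change already reached at the last recorded visit. The documents give none of these by arm, so they are assumptions. Assume also that leavers would otherwise have followed their arm's planned course. Then:

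expected difference = 15 × [(1 − d_L) + d_L f] − 6.35 × [(1 − d_P) + d_P f]

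| Loss, Longmu Tang / placebo | f = 0 | f = 0.5 |
|---|---|---|
| 20% / 20% | 12.00 − 5.08 = 6.92 | 13.50 − 5.715 = 7.785 |
| 30% / 10% | 10.50 − 5.715 = 4.785 | 12.75 − 6.0325 = 6.7175 |
| 10% / 30% | 13.50 − 4.445 = 9.055 | 14.25 − 5.3975 = 8.8525 |

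Subtracting 8.65 gives the error as −(1 − f) × (15 d_L − 6.35 d_P). It is zero only if f = 1, or if d_P = (15 / 6.35) × d_L, about 2.36 times the Longmu Tang loss. Below that ratio the difference shrinks; above it, the difference is inflated.

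**4. Imputation on the same footing.** A large-sample simulation assumed linear mean improvement, visits read as weeks 1, 2, 4, 6 and 8, and dropout either unrelated to the scores or dependent only on observed ones, with about 18–30% lost per arm. The last-value rule gave 7.44 to 7.79 against a true difference of 8.63 to 8.65. Regression imputation from the earlier visits gave 8.63 to 8.65. That was conditional-mean imputation standing in for multiple imputation, and the result holds only because the data were missing at random by construction.

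**5. The adjoining sentence.** The group defined in {11b} includes users of prohibited drugs. Their last recorded data are first included and then, in the next sentence, declared invalid. Reconciling {11b} with {20c} on non-completers alone would leave this unresolved.

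**The case against.** The strongest reply is that {11b} never speaks of carrying a value forward and does not mention week 8. It may mean only that data collected before withdrawal are kept. That would fit multiple imputation, which uses those earlier scores, and {20c}, the section assigned to missing data, names no other method. This reading is possible. A reader might infer that the two rules cannot both apply, or that the trial has adopted last-value substitution; the documents do not establish either. But {11b} singles out the last data rather than all data, in a trial with several scheduled SCORAD assessments, so substitution remains the plain reading. Under either meaning the sentence needs rewording.

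The size is also open to challenge. The largest loss of effect needs 30% loss on Longmu Tang against 10% on placebo, whereas the Interim analyses section reports no adverse events in the pilot and earlier studies, and withdrawal for poor efficacy would more plausibly raise placebo loss. In the 10% / 30% case the error is only 0.2 to 0.4 points, small beside an SD of 8.69. Equal loss shrinks the difference, which is conservative for a superiority claim. All of this stands, and it is why the figures are illustrations and not forecasts.

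Finally, 8.65 is the right benchmark only if leavers would have followed their arm's planned course. An intention-to-treat effect that includes children who stopped treatment may differ from it, and multiple imputation is itself biased if withdrawal depends on unobserved worsening. Both limits stand. They qualify the size but do not remove the conflict.

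**Conclusion.** The concern holds in this form: on the plain reading of {11b}, the article gives two different rules for the same missing week-8 SCORAD values, up to about 12 of 60, and does not say which is primary. If substitution is used, the estimate is generally biased, by an amount and in a direction that depend on the timing and balance of loss. In the cases shown the planned 8.65 became anything from about 4.8 to 9.1. Those figures rest on the assumed loss splits, on 0–50% of change reached, and on leavers otherwise following the planned course. Multiple imputation is the better primary rule, being already stated and less open to bias here, but it is unbiased only under missing-at-random with an adequate model.

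Two stronger readings should be avoided. A reader might infer that the plan's estimate is biased outright; that follows only if substitution is what {11b} means and what is done. A reader might also infer that substitution makes standard errors too small; nothing in the documents shows this, and mixing early and late values can also widen the spread within an arm.

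**What to change.** Reword {11b} to say that all SCORAD data recorded before withdrawal are retained and used, and that missing week-8 SCORAD in the primary intention-to-treat analysis is handled by multiple imputation as in {20c}, using baseline and the interim SCORAD values already scheduled. Label any last-value substitution as a sensitivity analysis only. Do not simply delete the sentence, since that would lose the commitment to keep pre-withdrawal data.

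Reconcile the following sentence, on participants who used prohibited drugs, with the same rule, so that it is clear whether their data enter the intention-to-treat analysis and how any resulting gaps are treated.

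The cost is a few sentences of protocol wording and a few lines of analysis code. No new assessments and no change in sample size are needed. The wording should be fixed before the blind is broken.

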#### Inclusion criteria

Clinical diagnosis of ADClinical diagnosis for TCM syndromes of damp-heat disturbing heart-mindScoring Atopic Dermatitis (SCORAD) score between 0 and 50Age 6–12 yearsThose who volunteered to participate in clinical trial observation and signed the informed consent formThose compliant with treatment completion and follow-upNo intake of concomitant drugs during the observation period, except for those specified

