#### Relevant concomitant care permitted or prohibited during the trial {11d}

Participants will be discouraged from receiving any other treatment or medication during the study period to prevent any effect on the results. During treatment, if there is substantial exudate or severe itching, the patient will be allowed to moisten the exudate area with the Pifukang solution (specification 50 mL/bottle, national medicine quasi-word Z19990045; Beijing Huayang Kuilong Pharmaceutical Co., Ltd.) 2–4 times a day. An eight-layer medical gauze will be dipped into the diluted lotion, which has been diluted six times with cooled boiled water at 4–10°, gently wrung out, and then applied to the affected skin. Loratadine tablets (Caretan, specification 10 mg × 6 tablets, national medicine quasi-word H10970410; Bayer Medicine (Shanghai) Co., Ltd.) will also be allowed to be taken orally once a day, 10 mg each time, if itching is difficult to resist. Details of the prescriptions and medications used will be recorded in the CRF. The proportion of participants using rescue drugs will be compared between the two groups. The use of other TCMs is prohibited.

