### Statistical methods

#### Statistical methods for primary and secondary outcomes {20a}

Data analysis will be completed using the Statistical Package of Social Sciences software (version 22.0; IBM Corp.), according to the per-protocol and intention-to-treat principles. Normally distributed continuous variables will be reported as mean ± standard deviation, and non-normally distributed continuous variables will be reported as median (interquartile range). The two-independent sample *t*-test, Wilcoxon test, or paired *t*-test will be used to analyse continuous variables, and the chi-square test and Fisher exact probability test will be used to analyse categorical variables. The two-sided test will be used uniformly in the hypothesis testing. A *P-*value < 0.05 will indicate that the difference is statistically significant, and a *P*-value < 0.01 will indicate that the difference is highly statistically significant.

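### The rule voiding prohibited-drug users' data contradicts the sentence before it and the intention-to-treat analysis; it should be deleted or confined to the per-protocol set

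*Protocol article*

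**What the plan says.** Section {11b} of the protocol article opens with a group it defines as "Participants who fail to complete the study for various reasons or use prohibited drugs in the protocol, regardless of the time or reason"; these participants may leave the study. After a sentence on reporting serious adverse events, it says of them: "The last recorded data for these participants will be included in the data analyses". The next sentence reads: "Data obtained from participants who used prohibited drugs in the protocol will be treated as invalid".

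The drop-out criteria list use of prohibited drugs beside voluntary withdrawal (for example for poor efficacy or adverse reactions) and loss to follow-up.

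Section {20a} says the data will be analysed "according to the per-protocol and intention-to-treat principles". Section {20c} says that participants with poor adherence (drug compliance below 80%), or who are off medication and testing, "will be included in the intention-to-treat analysis and excluded from the per-protocol analysis". It adds: "A multiple data imputation procedure will be used to impute the missing data". It makes no exception for prohibited-drug users.

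Section {11d} permits two rescue treatments, a topical solution and loratadine, prohibits other TCMs and discourages any other treatment. On rescue it says: "The proportion of participants using rescue drugs will be compared between the two groups".

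**The concern.** Intention-to-treat compares participants as randomised, whatever happens afterwards. Taking a prohibited drug happens afterwards. A rule that voids a child's data for that reason changes who or what is compared, by a criterion that may differ between arms and may be related to outcome. With 30 children per arm, a few such cases matter.

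There is also a practical problem. Two adjacent sentences in {11b} give opposite instructions for the same children: one includes their last recorded data, the other treats their data as invalid. An analyst cannot follow both, and the text leaves room to choose once results are known.

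**Working it through.** **1. The instructions for a prohibited-drug user, side by side**

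| Source | Instruction |
|---|---|
| {11b}, sentence on last recorded data | Include what was last recorded |
| {11b}, next sentence | Treat the data as invalid, with no set or time point given |
| {20a} | Analyse by intention-to-treat and by per-protocol |
| {20c} | Keep non-adherent children in intention-to-treat, exclude them from per-protocol only, impute what is missing |

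The text allows at least three datasets:

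- (a) The whole record is voided and the child leaves the analysis. This is not intention-to-treat.
- (b) Only values after the drug use are set to missing and imputed. Every child stays, but observed outcomes are replaced by model draws.
- (c) The last recorded data are used.

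The difference between (a) and (b) is real. The participant timeline {13} schedules SCORAD at baseline and at several later visits. Under (b) the earlier scores can inform the imputation. If the whole record is void, those scores are lost too.

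**2. The plan's own figures**

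From the sample size section {14}: mean reductions of 15 and 6.35, SD 8.69 in both arms, alpha 5%, power 90%. Section {20a} makes tests two-sided.

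- Difference: 15 − 6.35 = 8.65. Standardised: 8.65 / 8.69 = 0.995.
- Two-sample t-test (noncentral t): 22.2, so 23 per group and 46 in total, as stated. Power at 23 per group is 91.0%.
- Loss to follow-up: 46 / (1 − 0.20) = 57.5, so 58; the stated 60 is this rounded up.

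No stated figure is in dispute.

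**3. Illustration A: 4 of 30 children voided in one arm only**

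The article gives no rate of prohibited-drug use, so the 4-versus-0 split is an assumption. So is a SCORAD change of zero in those four. Mean of the rest = (30 × arm mean − 4 × 0) / 26.

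- Placebo arm: 30 × 6.35 / 26 = 190.5 / 26 = 7.33. Difference 15 − 7.33 = 7.67, or 7.67 / 8.65 − 1 = −11%.
- Placebo arm, if the four had instead worsened by 5 points: (190.5 + 20) / 26 = 8.10. Difference 6.90, or −20%.
- Longmu Tang arm: 30 × 15 / 26 = 17.31. Difference 17.31 − 6.35 = 10.96, or +27%.

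**4. Illustration B: the worst-responding fraction q removed from each arm**

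Assume normal reductions with SD 8.69. Removing the lowest fraction q raises the mean of the rest by 8.69 × φ(z_q) / (1 − q). This is 0.94 for 5%, 1.69 for 10% and 3.04 for 20%.

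- 10% of placebo, 5% of active: 8.65 + 0.94 − 1.69 = 7.90.
- 20% of placebo, 5% of active: 8.65 + 0.94 − 3.04 = 6.55.
- 10% of each: 8.65 + 1.69 − 1.69 = 8.65, no bias.

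The cancellation in the last line depends on removing the same relative tail from arms with equal spread. If equal numbers were removed at the same absolute change, as in illustration A, it would not be exact: four zero-change children from each arm give 17.31 − 7.33 = 9.98.

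**5. Precision**

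Voiding data also costs power. At the planned effect it is 86.6% with 20 analysable children per arm and 82.7% with 18.

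**The case against.** The best defence is that invalid need not mean removed. Read with the sentence before it, the rule might mean that data up to the drug use are kept and later data are set aside. With the multiple imputation in {20c}, every randomised child would then stay in the set. That is a recognised approach, and the article does not exclude it. But it does not state it either: the sentence carries no time limit and no analysis set, and observed outcomes would still be thrown away. The ambiguity stands, and so does the need to resolve it.

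The defence does dispose of several stronger inferences that a reader might draw.

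- That {11b} voids everything, whenever and for whatever reason. The words about time and reason govern leaving the study, not the invalidity sentence.
- That the worst-controlled children leave the primary comparison. No reason for, or rate of, prohibited-drug use is given. Children with marked exudate or itching may use the permitted rescue treatments without falling under the rule, and rescue use is compared between arms. The link to treatment failure is plausible but inferred.
- That children could be declared ineligible afterwards, because the inclusion criteria bar "intake of concomitant drugs during the observation period, except for those specified". Nothing provides for retrospective ineligibility; the drop-out criteria treat such children as drop-outs.
- That the plan is at fault for not naming intention-to-treat or per-protocol as primary. That choice is commonly left to the statistical analysis plan, which is not shown.

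**Conclusion.** The contradiction is established from the text alone. The invalidity sentence in {11b} is unqualified, conflicts with its neighbour, and conflicts with {20a} and {20c}. Applied as written to all analyses, it makes the intention-to-treat analysis something else. This does not depend on why children take prohibited drugs.

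Neither the direction nor the size of bias can be determined. Illustration A spans 6.90 to 10.96 against a planned 8.65, but only by assuming four children in one arm, none in the other, and their outcomes. A reader might take −20% to +27% as the expected distortion; the article supports no such estimate. If drug use follows poor response and is commoner on placebo, illustration B shows the difference shrinking, so the rule need not favour Longmu Tang. With equal removal of the worst responders and equal spread, there is no bias in the difference, only a loss of precision.

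**What to change.** In {11b}, delete the invalidity sentence or confine it to the per-protocol set. In {11b} and {20c}, state that participants who used prohibited drugs stay in the intention-to-treat analysis, in their allocated arm, with the SCORAD data collected from them, and that multiple imputation applies only to data that are actually missing. Reword the sentence on last recorded data to agree, so that one rule covers these children. The list of prohibited and permitted treatments is not affected.

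If the investigators prefer to set values after prohibited-drug use to missing and impute them, that should be written down as such, with the time point and the analysis named.

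The cost is a few sentences of wording and continued outcome visits for the few children concerned. The sample size does not change.

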#### Secondary outcomes

The change in the Children's Dermatology Life Quality Index (CDLQI) score [20] (from baseline to week 8): the CDLQI is the most commonly used life index score of dermatological quality. This study will recruit children aged 6–12 years, so the CDLQI score will be used. The total CDLQI score ranges from 0 (best) to 30 (worst), with 6 as the MCID [21].The change in the number cancellation test (NCT) score (from baseline to week 8): the NCT is a traditional method used to evaluate attention function; the NCT score will be measured before and after the treatment, respectively, for 3 minutes each time, including the NCT net score and cancellation error rate, number of times of correct cancellation (the greater the better), number of times of incorrect cancellation, and number of times of omitted cancellation (the less the better), which will be compared before and after treatment. Raw score = the number of times of correct cancellation; net score = raw score – (the number of times of incorrect cancellation + 1/2 of the number of times of omitted cancellation); error rate = (the number of times of incorrect cancellation + 1/2 of the number of times of omitted cancellation) / raw score × 100%.Participants’ expectations of the Longmu Tang granule will be assessed at baseline using the following two questions: “Do you think the Longmu Tang granule will be effective for treating the illness?” and “Do you think the Longmu Tang granule will be effective for relieving the related symptoms of AD?” The response options will be ‘yes’, ‘no’, or ‘unclear’.Integral TCM syndrome score (from baseline to week 8 and 12; the scores and details are presented in Tables 2 and 3). A scale of 0–6 points is used to score patients with AD according to the severity of clinical symptoms.Significantly effective: inhibition or complete suppression of primary and secondary clinical symptoms and reduction of the syndrome score by ≥ 95%Effective: significant improvement in clinical symptoms and reduction in the syndrome score by 70–95%Ineffective: improvement in clinical symptoms and reduction in the syndrome score by 50–70%Invalid: reduction of treatment syndrome score by < 50%Long-term control: the evaluation of long-term control will be based on the change in the SCORAD score and change in the CDLQI score from baseline to the end of the 8-week follow-up after treatment.

**Table 2 Tab2:** Traditional Chinese medicine syndrome score

	None	Mild		Moderate		Severe	

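### Section {11b} voids the data of randomised children who use prohibited drugs, without limiting this to the per-protocol set, which does not fit the planned intention-to-treat analysis

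*Protocol article*

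**What the plan says.** Section {11b} of the protocol article opens with one group made up of two kinds of participant: "Participants who fail to complete the study for various reasons or use prohibited drugs in the protocol". They may discontinue, and then: "The last recorded data for these participants will be included in the data analyses". The next sentence singles out the second kind: "Data obtained from participants who used prohibited drugs in the protocol will be treated as invalid".

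The section headed Drop out criteria lists use of prohibited drugs as a reason for drop-out, beside voluntary withdrawal and loss to follow-up.

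Section {20a} says that the data will be analysed "according to the per-protocol and intention-to-treat principles". Section {20c} says that participants with poor adherence and compliance below 80%, or who are no longer taking medication and being tested, "will be included in the intention-to-treat analysis and excluded from the per-protocol analysis". It adds: "A multiple data imputation procedure will be used to impute the missing data". It does not mention prohibited-drug use.

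The primary outcome is the change in SCORAD from baseline to the end of the 8-week treatment.

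**The concern.** Taking a prohibited drug happens after randomisation. A child whose eczema is not controlled has more reason to take one, so use may track response, and it may be commoner in the arm that is doing worse. Section {11d} recognises a similar mechanism for the permitted rescue drugs: it ties them to severe symptoms and plans to compare their use between the arms.

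If the data of such children are voided, the two groups that remain are no longer the groups that randomisation made comparable. Blinding does not prevent this, because selection through response needs no knowledge of the allocation. The primary SCORAD comparison would then carry the intention-to-treat label without being one.

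**Working it through.** **Step 1: the rules side by side for one child.** Take a child who uses a prohibited drug in week 5 and has a week-8 SCORAD measured.

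- Intention-to-treat, section {20a}: the child is analysed in the randomised arm.
- Section {11b}, voiding sentence: the child's data are invalid. No analysis set is named, and data from before week 5 are not spared.
- Drop out criteria: the child counts as a drop-out. If medication and testing then stop, section {20c} keeps the child in the intention-to-treat analysis and removes the child only from the per-protocol analysis.

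The first two rules cannot both be followed. The third shows how the plan treats other children who stop: they are kept.

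**Step 2: does the article give a size?** No. It states no rate of prohibited-drug use in either arm and no effect of such drugs on SCORAD.

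**Step 3: what the answer depends on, under assumed rates.** The only documented input is the standard deviation of 8.69 in the sample size section. That section's own figure reproduces: difference 15 − 6.35 = 8.65, 8.65/8.69 = 0.995, two-sided 5%, 90% power, two-sample t-test, giving 23 per group and 46 in total. It is not in dispute.

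Assume that the worst-responding fraction f of an arm is voided and that outcomes are normal. The mean reduction in that arm then rises by

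SD × φ(z_f) / (1 − f),

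where z_f is the f-quantile of the standard normal distribution and φ its density. With SD = 8.69:

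- f = 5%: 8.69 × 0.1031/0.95 = 0.94
- f = 10%: 8.69 × 0.1755/0.90 = 1.69
- f = 20%: 8.69 × 0.2800/0.80 = 3.04
- f = 30%: 8.69 × 0.3477/0.70 = 4.32

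With no true effect, the bias (Longmu Tang minus placebo) is the difference of two such shifts. Type I error comes from 20,000 simulated trials per row with 30 children per arm randomised. The last two columns weaken the link between outcome and voiding to a correlation of 0.5.

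| Assumed voiding, Longmu Tang / placebo | Bias, worst voided | Type I error | Bias, correlation 0.5 | Type I error |
|---|---|---|---|---|
| 10% / 10% | 0 | 5.1% | 0.02 | 5.1% |
| 0% / 10% | −1.69 | 11.5% | −0.85 | 6.3% |
| 5% / 20% | 0.94 − 3.04 = −2.10 | 16.8% | −1.07 | 7.0% |
| 10% / 30% | 1.69 − 4.32 = −2.62 | 24.6% | −1.32 | 8.3% |

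At the planned effect, the 5% / 20% row would shrink the expected difference to 8.65 − 2.10 = 6.55. Swapping the arms reverses every sign. The table therefore shows that both size and direction hang on quantities that the article does not give. It is not an estimate of the bias in this trial.

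**The case against.** The strongest reply is that *invalid* may have been meant harmlessly. It could mean invalid for the per-protocol set only, since both analyses are planned. Or it could mean set to missing, after which the multiple imputation of section {20c} keeps every child in the intention-to-treat set. Either is possible, and the second would soften the point. But the text says neither, and setting to missing still discards week-8 SCORAD values that were observed. Taken literally, it discards earlier values too, which the imputation would need. The article's other use of the word, "Invalid: reduction of treatment syndrome score by < 50", is a response category for the syndrome score and yields no SCORAD value.

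Four stronger readings are tempting and are not supported.

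- A reader might infer that section {11b} flatly contradicts itself, including and then voiding the same children. The second sentence can be read as an exception to the first. That rescues the section internally but leaves the clash with intention-to-treat.
- A reader might infer a direct contradiction with section {20c}. That section does not name prohibited-drug users. The link runs through the drop-out criteria, and a child who takes a prohibited drug but stays compliant and keeps attending falls outside its wording.
- A reader might infer that the prohibited drugs are left undefined. The inclusion criteria bar unspecified drugs and section {11d} names two that are allowed; a fuller list may stand in the full protocol.
- A reader might infer a material loss of power from "Considering a 20% loss to follow-up, this trial will require 60 participants (30 participants in each group". The article does not say whether voided children fall inside that 20%, and at the planning inputs power is 91.0% with 23 per arm and still 89.7% with 22.

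**Conclusion.** The point stands as a badly fixed rule. As written, section {11b} voids data from randomised children because of a post-randomisation event, with no limit to the per-protocol set, and this cannot be reconciled with the intention-to-treat analysis in section {20a}. It should be changed, because it bears on the primary comparison.

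The conclusion rests on the plain meaning of the voiding sentence. The risk of bias rests on the further assumption that prohibited-drug use may depend on response and differ by arm; this is plausible but not documented. A reader might go on to infer that the primary result will be biased, or biased in one particular direction. The article does not support that: if use is rare, unrelated to outcome, or balanced between arms with a similar link to outcome, the effect could be negligible.

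**What to change.** - **Section {11b}:** replace the voiding sentence with a rule that children who use a prohibited drug stay in the intention-to-treat analysis with their observed week-8 SCORAD, or with the multiple imputation of section {20c} if that value is missing, and are excluded from the per-protocol analysis only.
- **Section {11b}, sentence on last recorded data:** delete it or align it with section {20c}. Otherwise it could be taken as carrying the last value forward, beside multiple imputation, and two rules would govern one missing week-8 value.
- **Drop out criteria and section {11b}:** state that prohibited-drug use does not by itself end follow-up visits.
- **Section {20c}:** add use of a prohibited drug as a per-protocol exclusion, confined to drugs that the protocol prohibits, so that an unrelated medicine does not exclude a child.

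The cost is mainly wording, plus the remaining visits of children who would otherwise have been dropped. Medication use is already recorded in the case report form, and the sample size does not change. The downsides are a possibly smaller per-protocol set and an intention-to-treat estimate that includes whatever effect the prohibited drugs have. The change should be made before the blind is broken.
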